To the best of the researcher’s knowledge, there are very few prospective longitudinal studies in Thailand to account for the long-term response of CU treatment, clinical outcomes, and patient-reported outcomes (PROs) among people living with CU based on routine practice. As such, this study aim to develop the CORE-CU (Clinical Outcomes, Patient-Reported Outcomes, and Economic Burden for Thai People Living with Chronic Urticaria), a monocentric prospective cohort study, to better understand the long-term responses to treatment options and the disease burden in Thai CU patients.

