### Objectives

#### Primary objectives

To evaluate and track the treatment response and clinical outcomes among adult CU patients during routine urticaria care management.To assess the impact of CU on long-term PROs, including HRQOL, symptom burden, mental health issues, well-being, and psychosocial problems.

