### Study population

Adult patients in an outpatient urticaria clinic will be consecutively recruited for this research. The study population will consist of adult patients diagnosed with CU (duration >6 weeks) based on the EAACI/GA^2^LEN/EuroGuiDerm/APAAACI Guideline on urticaria [1]. Both CSU and CIndU are included (Table 1). The inclusion and exclusion criteria for the longitudinal cohort are shown in Table 2.

**Table 1 pone.0279566.t001:** Classification of chronic urticaria subtypes [1].

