**Chronic inducible urticaria (CIndU)**
• Symptomatic dermographism (urticaria factitia or dermographic urticaria)
• Delayed pressure urticaria (pressure urticaria)
• Solar urticaria
• Aquagenic urticaria
• Contact urticaria
• Cold urticaria (cold contact urticaria)
• Heat urticaria (heat contact urticaria)
• Cholinergic urticaria
• Vibratory angioedema

**Table 2 pone.0279566.t002:** Eligibility criteria of the CORE-CU study.

**Inclusion criteria**	**Exclusion criteria**
• Participants aged ≥18 years at the date of screening	• Any conditions (both mental or physical) that would interfere with the participant’s ability to comply with the study protocol
• Diagnosed with chronic urticaria based on the EAACI/GA^2^LEN/EDF/APAAACI guideline: had wheals and/or angioedema for >6 weeks	
	• The prognosis for survival <12 months
	• A primary skin disorder that could explain the pruritus or angioedema (i.e., cholestatic liver disease, atopic dermatitis, bradykinin-mediated angioedema, Bullous pemphigoid, Well’s syndrome, Schnitzler’s syndrome, etc.)
• Had an ability to understand and willingness to sign an informed consent statement	

Abbreviations: APAAACI, Asia Pacific Association of Allergy, Asthma and Clinical Immunology; CORE-CU, Clinical Outcomes, patient-Reported outcomes, and Economic burden for Thai people living with Chronic Urticaria; EAACI, European Academy of Allergology and Clinical Immunology; EDF, European Dermatology Forum (EuroGuiDerm); GA^2^LEN, Global Asthma and Allergy European Network; HIV/AIDS, human immunodeficiency virus/acquired immune deficiency syndrome.

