### Data collection and study schedule

The cohort will be collected and registered using the routine clinical practice data of adult patients with CU. Data will be embedded based on multiple datasets, including (i) electronic health records, outpatient and inpatient claims data, and routine laboratory results; (ii) the Support System Pharmacy Dispensing extract, an administrative data source on pharmacy dispensing that provides patient-level details on medication utilization, dispensing detail, and health care costs; and (iii) Urticaria Care Database via REDCap^TM^, which provides patient-level details on sociodemographic and clinical characteristics, long-term urticaria care and monitoring, and PRO measures.

Participant recruitment will be performed continuously during the observation period to identify patients who are interested in participating in the CORE-CU registered cohort. Eligible participants will be monitored based on routine practice every 3 months (medical history, physical examination, and health care costs; further laboratory tests during study follow-up are needed in the case of clinically indicated) based on in-center follow-up care. Regarding PROs assessment, urticaria symptoms responses using participant self-reported diaries tools will be assessed monthly-basis. While HRQOL and mental health issue aspects will be evaluated and collected every 3 months during the CU clinic follow-up care. All the participants will be monitored for as long as possible; however, eligible participants will be assessed for at least one year (Table 3). If possible, after completing a one-year follow-up, participants will be reassessed and monitored based on the schedule of observation and procedures in the first year manner. Ultimately, participants will be followed and censored until the date of the earliest incidence of death, withdrawal for any reasons, transfer to another center, or loss to follow-up; whichever occurred first.

**Table 3 pone.0279566.t003:** Schedule of observation and procedures.

Parameter	Study Period: Time (Month)													
	Screening -1	Assessment and Follow-Up												
		0	1	2	3	4	5	6	7	8	9	10	11	12
Check eligibility against inclusion/exclusion criteria and medication review	X													
Gathering informed consent		X												
Sociodemographic and lifestyle data		X												
Medical history and physical examination		X			X			X			X			X
Patient-reported outcomes/experiences														

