#### Statistical analysis

Preplanned statistical analysis will be performed based on one-year follow-up care (Table 3). The characteristics of the study cohort will be described as frequencies with percentages for categorical variables and mean ± standard deviation or medians with interquartile range for continuous variables as suitable. The differences between treatment groups (treatment-based non-sedating second-generation H1-antihistamines, biologics, or immunosuppressive agents) or severity strata of urticaria symptoms based on UAS7 (mild, 7–15 points; moderate, 16–27 points; and severe, 28–42 points) for categorical and continuous variables will be compared using Fisher’s exact test and analysis of covariance or Kruskal-Wallis test, respectively.

The point prevalence of adverse health outcomes (e.g., treatment responses [response vs. refractory to first-line therapy with non-sedating second-generation H1-antihistamines], symptoms controlled [uncontrolled, UCT <12 points vs. controlled, UCT ≥12 points], and occurrence of adverse mental health issues [including HRQOL impairment, depression, anxiety, insomnia, and somatic symptoms) will be estimated and reported corresponding to 95% confidence intervals (95% CIs). Subgroup analyses will be performed based on key patient characteristics (i.e., age of study participants, female sex, duration of CU, severity of urticaria symptoms, subtypes of CU, body weight/body mass index, total immunoglobulin E level, history of allergy or other systemic diseases, specific pharmacological treatments, and concomitant and rescue medications). In addition, one-year follow-up findings will be compared to assess the long-term response to the prevalence of adverse health outcomes. The overall trend analysis will explore the effect of over time across the cohort time frame.

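### The one-year change in prevalence is read as long-term response, but it starts at enrolment in a cohort open to new and established patients, so it partly reflects case mix

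*Protocol article*

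**What the plan says.** **Who enters.** Under Study population: "Adult patients in an outpatient urticaria clinic will be consecutively recruited for this research". The disease criterion in Table 2 is that the patient "had wheals and/or angioedema for >6 weeks", with no upper limit. Table 2 has no condition on previous treatment, new referral, stable therapy or current disease activity.

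**When the clock starts.** Under Data collection and study schedule: "Participant recruitment will be performed continuously during the observation period". Table 3 places consent and the first patient-reported outcomes at month 0. It ties month 0 neither to a treatment start nor to a first clinic visit.

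**What is compared and how it is read.** Under Statistical analysis: "one-year follow-up findings will be compared to assess the long-term response to the prevalence of adverse health outcomes". The sentence does not name the reference time. The Introduction gives the purpose as "to better understand the long-term responses to treatment options and the disease burden in Thai CU patients", and the first primary objective is "To evaluate and track the treatment response and clinical outcomes among adult CU patients during routine urticaria care management".

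**What is planned around it.** Treatment groups ("treatment-based non-sedating second-generation H1-antihistamines, biologics, or immunosuppressive agents") and UAS7 severity strata are compared. The subgroup list includes duration of CU, symptom severity, subtype, specific drug treatments, and concomitant and rescue medication. Change in outcome status is modelled by random-intercept logistic regression with individual-level and baseline predictors. Neither the subgroup list, which is worded as complete, nor the model description names time since first clinic visit or time since start of current therapy. The article describes no untreated or external comparator.

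**The concern.** A before-after change can be described as response most readily when every patient starts from the same point in care, such as the start of a drug. Here the starting point is the day of consent. For one patient that may be the first specialist visit, for another a change of therapy, and for a third a routine visit on a regimen unchanged for years. The treatment groups named in the plan make such a range of treatment stages likely.

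These patients have different expected courses over the next 12 months even under identical care. Pooling them gives an average whose size depends on how many of each kind enrol. If that average is reported as long-term response, a reader could credit treatment with a change that partly reflects who was recruited, or could take a cohort of mainly stable patients as evidence that treatment does little. The first primary objective concerns treatment response, so the label matters.

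**Working it through.** **1. The plan's own figure.** The only calculation in the plan is the target of 132. The precision formula for one proportion reproduces it at a prevalence of 17.2% (or its complement, 82.8%):

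- n = 1.96² × 0.172 × 0.828 / 0.10² = 54.7, rounded up to 55
- × design effect 2.0 = 110
- × 1.2 for 20% missing data = 132

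This is a calculation for one prevalence at one time. It has no input for a change between two times, so it neither supports nor contradicts the one-year comparison.

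**2. Effect of the mix.** Let f be the share of patients new to the clinic or changing therapy at month 0. The inputs are assumed: established patients are 40% uncontrolled at both times, and the others go from 80% to 40%.

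- Month 0 prevalence = 0.80f + 0.40(1 - f)
- Month 12 prevalence = 0.40
- Change = -0.40f

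| f | Month 0 | Month 12 | Change (points) |
|---|---|---|---|
| 0% | 40% | 40% | 0 |
| 25% | 50% | 40% | -10 |
| 50% | 60% | 40% | -20 |
| 75% | 70% | 40% | -30 |

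As a sensitivity check, take the ends of the range that the Sample size estimation section gives for inadequate response or uncontrolled symptoms. The new or changing patients then go from 82.8% to 28.7%, and the established patients stay at 28.7%. The change is -0.541f: 0, -13.5, -27.1 or -40.6 points for the same four shares. Using these ends in this way is also an assumption.

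**3. Regression to the mean.** Assume no true change, a long-run prevalence of 50%, and a bivariate normal score with correlation r between month 0 and month 12. Then q = P(uncontrolled at 12 | uncontrolled at 0) = 0.5 + arcsin(r)/π, which is 0.667 at r = 0.5 and 0.856 at r = 0.9.

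- *No link between entry and activity.* At r = 0.5, 33% of the uncontrolled become controlled and 33% of the controlled become uncontrolled. The net change is 0.5 × 0.333 - 0.5 × 0.333 = 0.
- *A share g enters only while uncontrolled.* The change is -g(1 - q). For g = 25% this is -8.3 points at r = 0.5 and -3.6 at r = 0.9. For g = 50% it is -16.7 and -7.2.

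**4. Compared with sampling error.** The 95% half-width of a paired change d with discordant share D is 1.96 × √((D - d²)/n). Take n = 132, or 106 after 20% loss (132 × 0.8 = 105.6), with D assumed at 30% to 50% and d at 10 to 27 points. The half-width is then about 8 to 13 points. The mix effect at f = 25% is of that order, and at 50% or more it is larger.

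**The case against.** The best defence is that the plan is descriptive. The objective speaks of tracking patients in routine care, the article never claims a causal effect, and treatment response has its own definition there (response versus refractory to first-line antihistamines, reported as a prevalence). The one-year sentence names neither month 0 nor a single pooled change. Any registry average depends on case mix. In the illustration, the fall from 80% to 40% could itself be treatment working. The planned subgroups and the model with baseline predictors already address part of the heterogeneity, and the full protocol, which is not shown, may classify patients at entry.

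Much of this stands. The month-0 reference and the mix of patients are inferences, though Table 3 and the open eligibility support them. The illustration shows dependence on mix; it does not show that treatment has no effect. The planned analyses do help, but only in part. Long-standing disease can be newly referred, and a treatment subgroup does not separate patients starting a drug from those stable on it. A subgroup chosen as severe at baseline is itself exposed to regression to the mean. The defence does not remove the stated reading of the comparison as long-term response, which is in the article itself.

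A reader might go further and infer that remission, first treatment and regression to the mean determine most of the change, that month 0 is a symptom peak, or that established patients enrol early and new referrals late. The article gives no share of new patients, remission rate, within-patient correlation, activity threshold or enrolment pattern, so it supports none of these. Nor does the one-third turnover in step 3 bias the pooled prevalence, because opposite transitions cancel it. It matters only where entry is linked to activity, or in analyses restricted to patients uncontrolled or severe at baseline.

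**Conclusion.** The point holds in a limited form. The plan reads an uncontrolled one-year comparison as long-term response, although enrolment can fall at any stage of care and entry status is not a named stratifier or covariate. The pooled change therefore depends partly on case mix. It cannot be separated from natural remission or, if patients enter because they are symptomatic, from regression to the mean.

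The true size is unknown. Under the assumed 40% and 80% inputs it runs from 0 to -30 points as the new or changing share goes from 0 to 75%, so it may be nothing or may exceed the sampling error. This is a weakness of interpretation with an inexpensive remedy. It does not invalidate the cohort or its prevalence estimates.

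**What to change.** 1. Derive entry status at month 0 from data already scheduled: the screening medication review, the month-0 history and medication record, the health records and the dispensing extract. Where numbers allow, keep three groups apart: (a1) new to the clinic, (a2) established but starting or stepping up therapy at that visit, and (b) established on unchanged therapy.
2. Report month-0 and month-12 prevalence, and the change with its 95% confidence interval, by entry status. State explicitly that month 0 is the reference.
3. Add entry status and its interaction with time to the random-intercept longitudinal model.
4. Describe the pooled figure as change under routine care, not as treatment response.

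The cost is one derived variable, one table split, one model term and a change of wording, with no new data collection. The article reports 75 patients enrolled by 10 August 2022 with enrolment still open, so the definition could be fixed before the one-year results are analysed. The downside is smaller groups and wider intervals. The split also does not by itself separate treatment effect from remission or regression to the mean within groups (a1) and (a2), and the report should say so.

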### Statistical analysis plan

#### Sample size estimation

The sample size of participants was estimated based on the prevalence of adverse outcomes among CU patients, including (i) inadequate response to a standard dose of H1-antihistamines or uncontrolled urticaria symptoms (UCT score <12) with a range of 28.7%–82.8% [3, 8, 12, 13]; (ii) HRQOL impairment (DLQI >10 points) with a range of 30.9%– 31.5% [7, 8]; and (iii) mental health and psychosocial problems (depression, anxiety, insomnia, and somatic symptoms) with a range of 17.2%–55.7% [6, 7, 9]. With respect to a design effect of 2.0 and missing data of 20%, a target of at least 132 CU patients will be required for this study to ensure a 10% of margin of error and 0.05 type I error. Nevertheless, there will be no restrictions on the number of participants in this prospective longitudinal study.

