For cross-sectional analyses, the crude association among participant characteristics will be explored using the univariable logistic regression models to identify the candidate risk factors for adverse health outcomes. Subsequently, candidate risk factors with a *P*-value of <0.100 will be included in the multivariable logistic regression analysis with the backward elimination method. The variance inflation factors of risk factors within the multivariable model will be investigated to detect the multicollinearity of the final model. The odds ratios (ORs) with 95% CIs will be reported as the effect estimates of the final set of risk factor models for adverse health outcomes. For longitudinal analyses, changes in the adverse health outcome status during the follow-up period will be analyzed using multilevel logistic regression models with random intercepts to explore the associations with individual-level and baseline predictors.

All analyses will be performed using Stata software (version 16.0; StataCorp LP). Statistical significance for all tests will be two-tailed, with a *P*-value of <0.05. For participants with missing covariates, multiple imputation methods will be used to analyze incomplete datasets. However, variables containing more than 20% of missing data will be excluded from all analyses.

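### Risk factors are chosen by univariable P-value and backward elimination on the data used to estimate them, and the surviving odds ratios are reported as effect estimates with conventional intervals

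*Protocol article*

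**What the plan says.** The cross-sectional part of the Statistical analysis section fixes the procedure. Each participant characteristic is tested alone in a logistic model, those with P below 0.100 "will be included in the multivariable logistic regression analysis with the backward elimination method", and variance inflation factors are examined in the final model. Then "The odds ratios (ORs) with 95% CIs will be reported as the effect estimates of the final set of risk factor models". The general two-sided significance level is 0.05; no separate elimination threshold is given. No shrinkage, internal validation or adjustment for selection is named.

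The candidate list is not closed. The same section says "Subgroup analyses will be performed based on key patient characteristics" and names ten entries, about 11 variables once a double entry is split. The list of data collected also covers sociodemographic items, medical history, medication and a long laboratory panel.

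The Sample size estimation section rests on the precision of a prevalence: "With respect to a design effect of 2.0 and missing data of 20%, a target of at least 132 CU patients will be required" "to ensure a 10% of margin of error and 0.05 type I error". It does not consider the number of model terms, and it sets no upper limit on recruitment.

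**The concern.** Screening and elimination keep the predictors whose estimates happened to be large in this sample. The same sample then supplies the odds ratios and intervals, which are computed as if the model had been fixed beforehand. Three consequences follow:

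- Some retained predictors have no true association.
- Weak true effects are overstated when they survive, and are often dropped.
- Variables that matter jointly but not alone can be lost at the screen.

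The variance inflation check addresses none of these. A reader of the final table could take a chance finding for a risk factor, or a modest association for a strong one.

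**Working it through.** **1. The plan's sample size.** For one proportion, n = 1.96² × p(1 − p) / d². With p = 0.172 and d = 0.10, n = 3.8415 × 0.1424 / 0.01 = 54.7, rounded up to 55. Times the design effect of 2.0 this is 110; times 1.2 for missing data it is 132. The stated target is reproduced at 17.2% (or its mirror image, 82.8%) and at no other stated prevalence.

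**2. Information for the models.** Evaluable patients at the minimum: 132 × 0.8 = 105.6. The smaller outcome class across the stated prevalences:

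| Prevalence | Events | Non-events | Smaller class |
|---|---|---|---|
| 17.2% | 18.2 | 87.4 | 18 |
| 28.7% | 30.3 | 75.3 | 30 |
| 31.5% | 33.3 | 72.3 | 33 |
| 50% | 52.8 | 52.8 | 53 |
| 55.7% | 58.8 | 46.8 | 47 |
| 82.8% | 87.4 | 18.2 | 18 |

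**3. Chance of keeping a null predictor.** The procedure was simulated, 400 runs per setting (Monte Carlo standard error about 0.025), with independent candidates, the screen at P < 0.10 and elimination at 0.05. The elimination threshold is an assumption, taken from the general significance level. All candidates are null:

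| N, prevalence | 11 candidates | 24 candidates |
|---|---|---|
| 106, 17.2% | 0.39 | 0.67 |
| 106, 31% | 0.42 | 0.69 |
| 106, 44.3% | 0.41 | 0.70 |
| 132, 31% | 0.42 | 0.70 |
| 230, 31% | 0.40 | 0.69 |

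The formula 1 − 0.95^K gives 0.43 for K = 11 and 0.71 for K = 24. Sample size and prevalence hardly matter; the number of candidates does. With 25 candidates, one of them true, a separate simulation at N = 106 and 31% gave 0.69. If three of the 11 candidates have a true odds ratio of 1.5, only eight are null and the chance falls to 0.28–0.34 (1 − 0.95^8 = 0.34).

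**4. Overstatement of true effects.** Three true predictors, each with odds ratio 1.5 per SD; median odds ratio when selected:

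| N, prevalence | 11 candidates | 33 candidates |
|---|---|---|
| 106, 17.2% | 2.11 | 2.20 |
| 106, 31% | 1.89 | 1.95 |
| 106, 44.3% | 1.81 | 1.86 |
| 132, 31% | 1.76 | 1.82 |

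A true predictor of this size survived in only 28% to 52% of runs. For stronger effects the bias is small. A true odds ratio of 2.0 averaged 2.25 when selected (N = 106, 15 candidates, 31%) and 2.10 (N = 132, 11 candidates, 50%); a true 2.5 averaged 2.74 in the first of these settings.

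**5. Interval coverage for selected true effects.** With an odds ratio of 1.5, coverage was 0.89–0.92 at 17.2% prevalence (about 18 events) and 0.93–0.96 at 31% or 44.3%. With odds ratios of 2.0 or 2.5 at 31% it was 0.96.

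**6. Comparison with fixed models.** N = 106, one true odds ratio of 1.5:

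- 15 candidates with screening and elimination: 48–49% of final models keep a null predictor, and the selected odds ratio averages 1.9–2.2.
- All 15 terms fixed, no selection: 57–59% of models show at least one significant null.
- Six terms fixed: 20–22% show one, and the true odds ratio averages 1.55–1.60.
- Six candidates at 31% with screening and elimination: 19%, about the same as six fixed terms.

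So the shorter list lowers the false-factor rate, and fixing the terms removes most of the overstatement.

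**The case against.** The best defence is that the analysis is exploratory. The Objectives section lists treatment response and clinical outcomes, patient-reported outcomes, the clinical utility of those instruments, and economic burden; risk-factor identification is not among them. The screen is worded as exploration of candidates, and selection is confined to the cross-sectional analyses; the longitudinal multilevel model is described without a selection step. This stands, and it limits the importance of the point. It does not cover the final odds ratios, which the plan calls effect estimates without qualification.

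It is also fair that the false-factor rate comes from testing many candidates: a fixed model with all 15 terms does no better. Dropping selection while keeping a long list would not help.

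A reader might go further and infer that only 18 to 33 events will face dozens of candidates, so that false risk factors are certain and the intervals are generally too narrow. The document does not support that:

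- 18 to 33 covers prevalences of 17.2% to 31.5% only. Elsewhere in the stated ranges the smaller class reaches about 53.
- The target is a minimum, and missing covariates are to be imputed, so 106 is a cautious figure. Against this, the Cohort status section reports only 75 participants by August 2022.
- Dozens of candidates is a reading of the data-collection list, which names participant characteristics and laboratory data side by side. The plan does not say that every laboratory item will be screened, and it drops variables with more than 20% missing.
- The risk is a probability per model. Coverage of selected true effects is near nominal outside the sparsest setting; the intervals that fail are those of retained null predictors, which exclude 1 by construction.

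**Conclusion.** The point holds as an improvement to a secondary analysis. The document itself fixes a data-driven selection method and presents its output as effect estimates with ordinary intervals. At the minimum size, about 40% of final models would keep at least one null predictor if the roughly 11 key characteristics are screened and none is truly associated, and about 70% with 25 candidates. Selected weak effects would be overstated by an amount that matters for interpretation; strong effects only slightly.

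These figures assume independent candidates, elimination at 0.05 and about 106 evaluable patients. A larger cohort reduces the overstatement but leaves the false-factor rate almost unchanged.

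It would be wrong to infer that the cohort's main findings are at risk. The prevalence estimates, their intervals and the descriptive results do not pass through this procedure.

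**What to change.** For each adverse outcome, replace screening and elimination with one model specified before analysis. Choose about six terms on subject knowledge from the key characteristics in the Statistical analysis section, for example age, sex, disease duration, urticaria subtype, body mass index and baseline activity. Leave out any characteristic that helps to define the outcome being modelled. Keep all terms whatever their P-values, and use Firth penalisation when the smaller outcome class is small.

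If a wider screen is still wanted, report it separately as hypothesis-generating, and do not present its odds ratios and intervals as effect estimates.

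This changes analysis wording only: no new data, visits or patients are needed. Enrolment was still open at the reported cohort status, so the change can be made before analysis. The cost is that fewer predictors are examined in each model.

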#### Informed consent, autonomy, and confidentiality

Written informed consent will be obtained from all participants before they are included in the study. The participants’ consent will be obtained by trained research assistants. Based on the International Conference on Harmonization: Thai Guideline for Good Clinical Practice, a thumbprint is obligatory when a participant is illiterate. All participants have the right to leave a specific question unanswered or withdraw informed consent at any time for any reason during the study period. Data collected prior to study withdrawal will be considered for participants who discontinue. A written lay statement will be provided to inform them that the decision not to participate in the study will not affect following clinical care at the study site. No gifts or other payments will be offered.

Data gathered are stored in the study database without identifiers, and linking information is kept separate in a locked filing cabinet. The unique identifiers will be generated, completely encrypted, coded, and will be recorded as double-entry for use, principally for statistical analysis purposes using computer software. Additionally, the collected data will remain confidential and shared only with authorized research members.

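### The rule dropping any variable with more than 20% missing data does not exempt outcomes or pre-specified factors, and its cut-off equals the plan's own missing-data allowance

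*Protocol article*

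**What the plan says.** The last paragraph of the Statistical analysis section plans multiple imputation for participants with missing covariates. The next sentence opens with *However* and says that "variables containing more than 20% of missing data will be excluded from all analyses". It names no exempt variable, no denominator and no alternative for a variable over the limit.

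The Sample size estimation section carries the same percentage. It works "With respect to a design effect of 2.0 and missing data of 20"% and concludes that "a target of at least 132 CU patients will be required for this study". The precision aimed at is 10 points either side, with alpha set at 0.05. The section does not say to which visit or variable the 20% applies.

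Three other parts of the article bear on the rule:

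- The primary objectives concern treatment response and long-term patient-reported outcomes. The Statistical analysis section compares adverse-outcome prevalence at one year and fits a random-intercept logistic model to outcome status over follow-up.
- Table 3 schedules 15 self-reported measures up to month 12, four of them monthly. The data collection section foresees death, withdrawal, transfer and loss to follow-up. The consent section adds: "All participants have the right to leave a specific question unanswered".
- The subgroup factors are listed in advance and include total immunoglobulin E, duration of disease and body mass index.

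**The concern.** A cut-off on the missing percentage takes no account of what a variable is for. Read literally, the rule reaches outcomes. A month-12 control or quality-of-life score with 21% missing would leave every analysis, while one with 19% missing would be analysed in full. The design already accepts missingness at that level, and the late visits, where it is likely to be greatest, are those that the long-term objectives depend on. The planned multilevel model can use whatever visits a patient has, so the rule would discard information that the plan can otherwise use.

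Read as covariates only, the rule leaves outcomes alone. It still withdraws the planned imputation from the covariates with the most missing data and can delete a subgroup factor that was named in advance. Whether imputation is sound depends on why data are missing and on the imputation model, not on the percentage alone. Omitting a real confounder can bias adjusted associations.

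With both readings open, the choice between them could fall after the missing fractions are known.

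**Working it through.** **Inputs**

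- Exclusion limit: more than 20% missing (Statistical analysis).
- N = 132, margin 10 points, alpha 0.05, design effect 2.0, allowance 20% (Sample size estimation).
- Anticipated prevalences (same section): "uncontrolled urticaria symptoms (UCT score <12) with a range of 28.7%–82.8"% and "depression, anxiety, insomnia, and somatic symptoms) with a range of 17.2%–55.7"%.
- True missing rate of a month-12 outcome: not given in the document. It is assumed here, from 10% to 25%.

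**1. The plan's own figure**

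n = 1.96² × p(1 − p) / 0.10². The article does not say which p was used. With p = 0.172 (or 0.828, which has the same variance), n = 3.8416 × 0.1424 / 0.01 = 54.7, rounded up to 55. Then 55 × 2.0 = 110 and 110 × 1.2 = 132. The stated target is reproduced.

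Multiplying by 1.2 leaves 110 patients after a loss of 22, and 22/132 = 16.7%. Allowing for a full 20% loss would need 110/0.8 = 137.5, that is 138. So 132 in fact covers 16.7% missing, and that rate is included below.

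**2. Chance that one month-12 variable is dropped, counted per visit**

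0.20 × 132 = 26.4, so 27 or more missing values trigger exclusion. With X ~ Binomial(132, q), the chance is P(X ≥ 27):

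| Assumed true missing rate q | Chance of exclusion |
|---|---|
| 10% | 0.03% |
| 15% | 5.6% |
| 16.7% | 14.7% |
| 18% | 26.3% |
| 20% | 48.3% |
| 22% | 69.8% |
| 25% | 90.7% |

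**3. Other cohort sizes**

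Recruitment is not capped. At q = 20% the chance is 43% for N = 75, 50% for N = 138, 46% for N = 200 and 47% for N = 300. A larger cohort makes the change around the limit steeper (at N = 300, 16% at q = 18% and 78% at q = 22%) but does not remove it.

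**4. Missingness pooled over visits**

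Assume linear dropout reaching 20% at month 12. Over visits 0, 3, 6, 9 and 12 the average is (0 + 5 + 10 + 15 + 20)/5 = 10%, well below the limit. The pooled average is half the final rate, so month-12 dropout would have to be about 40% before it reached 20%. The undefined denominator therefore decides whether the rule is likely to apply at all.

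**5. Several outcomes together**

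The month-12 questionnaires fall at the same visit, so a patient who has left the study is missing on all of them. If missingness is fully shared, the chance of losing any outcome equals the chance of losing one (26% at q = 18%, 48% at q = 20%), and when it happens all are lost together.

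**The case against.** The strongest objection concerns scope. The rule is tied by *However* to a sentence about imputing covariates, and its natural purpose may be to limit that imputation. On that reading no outcome is dropped and the table in the working does not apply to outcomes. The reading is plausible, but the sentence speaks of variables and of all analyses without qualification. A reader might infer that outcomes are certainly covered; the text does not settle it.

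The second objection is that the 20% is a general sample-size allowance and not a forecast for month 12. The study also plans reminders, case managers and completeness checks. This stands. A reader might infer a coin toss for each key outcome, but that holds only if true missingness is very close to 20% and is counted per visit. At 15% the risk is small.

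Three further inferences are tempting and are not supported:

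- That losing at least one of many month-12 measures is nearly certain. This needs independent missingness across measures, which shared dropout contradicts.
- That the rule is outcome selection after the data are seen. The threshold is fixed beforehand and depends on completeness, not on results. What is left open is the reading and the denominator.
- That dropping a covariate biases every adjusted estimate. The models are exploratory risk-factor models with P-value screening and backward elimination and no designated exposure, so the most that can be said is that bias can arise. Routine laboratory tests are scheduled at month 0, so attrition would not explain missing immunoglobulin E, and nothing in the article shows that it would pass 20%.

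Finally, the article condenses a fuller protocol. That excuses missing detail, but here the article states a rule, and the fault is in the rule.

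**Conclusion.** The concern holds in a limited form and should be fixed. The rule discards variables on a missing percentage alone, does not exempt outcomes or pre-specified factors, and does not define its denominator. Its limit equals the plan's own allowance.

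If the rule reaches outcomes and is applied per visit at N = 132, the chance of losing a month-12 outcome runs from about 6% at 15% missing, through 15% at 16.7% and 26% at 18%, to 48% at 20% and 70% at 22%. These missing rates are assumptions. Shared dropout means that several one-year outcomes could be lost at once. If missingness is pooled over visits, exclusion of an outcome is unlikely at such rates. If the rule covers covariates only, outcomes are safe, but pre-specified factors can still be deleted where imputation was planned, and adjusted associations can be biased as a result.

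**What to change.** - Exempt outcomes, the pre-specified subgroup factors and the pre-specified covariates from the exclusion rule.
- Analyse outcomes with the planned multilevel model on all available visits, whatever the missing fraction, and report that fraction.
- Impute pre-specified covariates, with the outcome and earlier scores in the imputation model.
- Confine any percentage cut-off to non-essential exploratory variables, and state whether it is counted per visit or over all visits.

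The cost is a change of analysis wording, slightly more imputation work, and reliance on a missing-at-random assumption for variables with more missing data. The sample size and data collection do not change. The Cohort status section reports enrolment still under way, with 75 patients, so the wording can be settled before the one-year analysis.
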